## Abstract

**Background::**

Ventriculoperitoneal shunt (VPS) surgery remains the most widely accepted and used option method to treat post-hemorrhagic hydrocephalus (PHH) worldwide while lumboperitoneal shunt (LPS) serves as an effectively alternative treatment. However, the outcomes of VPS and LPS in the treatment of PHH have not been compared in a prospective trial.

**Methods and design::**

In this monocentric, assessor-blinded, non-randomized controlled trial, 75 eligible patients with PHH for each group will be recruited to compare the outcomes of VPS cohort with that of LPS cohort. Each participant is evaluated before surgery, at the time of discharge, 3, and 6 months after surgery by experienced and practiced assessors. The primary outcome is the rate of shunt failure 6 months after shunt surgery. The secondary measure of efficacy is National Institute of Health stroke scale, together along with Glasgow coma scale, modified Rankin Scale, and Evans index at the evaluation point. A favorable outcome is defined as shunt success with an improvement of more than 1 point in the National Institute of Health stroke scale. Complication events occurring within 6 months after surgery are investigated. A serious adverse events throughout the study are recorded regarding the safety of shunts.

**Discussion::**

The results of this trial will provide evidence for the treatment options for patients with PHH.

## Introduction

1

Post-hemorrhagic hydrocephalus (PHH) is featured as the ventriculomegaly as a result of intraventricular hemorrhage (IVH), intraparenchymal hemorrhage, or subarachnoid hemorrhage (SAH) occurring secondary to traumatic brain injury (TBI) or hemorrhagic stroke.^[1–3]^ PHH could increase the intracranial pressure and damage periventricular white matter leading to neurological function defects, however, the pathogenesis remains controversial to date.^[1]^ Early studies suggested obstruction of intraventricular cerebrospinal fluid (CSF) flow induced by blood clot or fibrin was contributed to the occurrence of PHH while recent study indicated that inflammation-associated CSF hypersecretion of choroid plexus epithelium leaded to PHH.^[4]^ Despite of the debates, surgical intervention through CSF diversion remains the standard treatment for patients with PHH. CSF shunts, including ventriculoperitoneal shunt (VPS) and lumboperitoneal shunt (LPS), and endoscopic third ventriculostomy (ETV) remain the main treatment options, efficiently alleviating the symptoms immediately after surgery. VPS surgery is the most widely accepted and used option to treat PHH worldwide while LPS and ETV serve as effectively alternative treatments.^[5,6]^ However, the optimal treatment is still controversial.

With the emergence of neuro-endoscopic technologies in the1990s, a great deal of attention was given to the application of ETV for hydrocephalus, particularly non-communicating hydrocephalus.^[5]^ But the indications for performing ETV have recently broadened to communicating types of hydrocephalus.^[5]^ Based on the results of a randomized controlled trial, VPS is the superior method as a result of better neurological outcomes and lower incidence of severe complications while comparing to ETV.^[7]^ LPS, diverting the accumulated CSF from spinal subarachnoid space to peritoneal cavity, has some advantages over VPS, particularly the avoidance of brain injury, which promoted Japanese Neurosurgeons approval it as the first-line treatment for patients diagnosed as idiopathic normal pressure hydrocephalus (INPH).^[8–10]^ However, a prospective trial in Japan that analyzed the outcomes of patients with INPH treated by LPS and compared with a historical VPS control suggested the risk of shunt revisions of LPS was higher than that of VPS (LPS vs VPS: 7% vs 1%) at 1 year after surgery.^[8]^ To date, no completed prospective trials has compared VPS with LPS in the treatment of PHH.

## Methods and design

2

### Objective

2.1

In this trial, we will evaluate the efficacy and safety of CSF shunts in the treatment of PHH. The objective of this trial is to compare the outcomes of VPS cohort with that of LPS cohort.

### Study design

2.2

The Shunting Outcomes of Post-hemorrhagic Hydrocephalus: Phase I (SOPH-1) is a monocentric, assessor-blinded, non-randomized controlled trial. 75 eligible participants for each group would be recruited. Neurosurgeons with extensive experience in the procedure conduct both types of shunt implantation. Each participant is evaluated before surgery, at the time of discharge, 3, and 6 months after surgery by experienced and practiced assessors. The primary outcome is the rate of shunt failure 6 months after shunt surgery. The secondary measure of efficacy is National Institute of Health stroke scale (NIHSS), together along with Glasgow coma scale (GCS), modified Rankin Scale (mRS), and Evans index at the evaluation point. A favorable outcome is defined as shunt success with an improvement of more than 1 point in the (NIHSS). Complication events occurring within 6 months after surgery are investigated. A serious adverse events (SAEs) throughout the study are recorded regarding the safety of shunts.

### Recruitment and eligibility

2.3

Participants would be recruited on outpatient department of West China Hospital of Sichuan University since June 2020. As shown in Figure 1, once the participants are determined to be a potential candidate for shunt implantation, they would be admitted and performed a lumbar puncture in the lateral recumbent position to demonstrate the communication of the ventricles with the spinal subarachnoid space and test the CSF opening pressure. Each subject will receive financial compensation.

**Figure 1 F1:**
[figure not shown]
Flow chart of the selection of patients. CSF = cerebrospinal fluid, GCS = Glasgow coma scale, mRS = modified Rankin scale, LPS = lumboperitoneal shunt, NIHSS = National Institute of Health stroke scale, VPS = ventriculoperitoneal shunt.

### Inclusion criteria

2.4

1.Adult (Age >=18 years);2.Evans index > 0.3;3.Onset secondary to subarachnoid hemorrhage, intraventricular hemorrhage or intraparenchymal hemorrhage;4.non-obstructive hydrocephalus;5.The communication of the ventricles with the spinal subarachnoid space is evident through lumbar puncture and CSF opening pressure is 70-200 mmH_2_O.

### Exclusion criteria

2.5

1.Idiopathic hydrocephalus;2.Congenital hydrocephalus;3.Obstructive hydrocephalus;4.Chiari malformation;5.CSF opening pressure is over 200 mm H_2_O or under 70 mm H_2_O;6.Decline to shunt implantation.

### Sample size

2.6

Previously published reports indicated that the rate of VPS failure is around 15.0% for adult patients with PHH, compared with a rate of 35.0% for LPS cohorts according to our previous study.^[11–14]^ We calculate that a sample of 70 will be required in this clinical trial with a significance level of 5% (2-sided) and a power of 80% to demonstrate a 20% difference in rate of shunt failure. Considering about the loss to follow-up, the sample size is enlarged to 75 for each group.

### Randomizing and blinding

2.7

Given consent for participation and met eligibility, patients would be assigned groups. The assignment will be performed according to self-selection or administrator selection rather than through randomization and is kept secret by the statisticians who are independent of this study. It is not possible to blind participants to allocation, but data collection teams and analysts are blind to allocation and the intervention clinicians will not participate in any assessment.

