### VPS

2.9

VPS implantation is conducted under general anesthesia and the patients are positioned in the supine position with the head turned to the left. Access to the lateral ventricle is obtained through scalp incision, skull drilling, and dura incision. Peritoneal access is obtained via a minimal invasive incision or split trocar access. A subcutaneous tunneler is passed from the abdominal incision to the cranial incision. The valve is placed at the cranial incision with a 3-point fixation to the subcutaneous tissue. Once the cranial catheter is connected to the valve and the valve is connected to the peritoneal tubing with confirmation of adequate CSF flow, the peritoneal catheter is inserted into the peritoneal space.

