### LPS

2.10

LPS implantation is conducted under general anesthesia and the patients are positioned in the lateral position. A lumbar catheter is inserted through the L3/4 or L2/3 interlaminar space into the spinal subarachnoid space. The catheter was then placed in a subcutaneous pocket made at the flank region. Peritoneal access is obtained via a minimal invasive incision or split trocar access. A tunneler is passed from the abdominal incision to the flank region, and then to the lumbar incision. The valve is placed at the frank region with a 3-point fixation to the subcutaneous tissue. Once the lumbar catheter is connected to the valve and the valve is connected to the peritoneal tubing with confirmation of adequate CSF flow, the peritoneal catheter is inserted into the peritoneal space.

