### Primary outcome

2.12

The primary outcome is the rate of shunt failure 6 months after shunt surgery. According to previous study, shunt failure is defined as the occurrence of clinical or radiological signs of shunt obstruction, breakage, tubing exposure, malfunction, or infection requiring shunt revision. Shunt success is defined as the absence of shunt failure.

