### Secondary outcomes

2.13

The secondary outcomes include NIHSS, CGS, mRS, and Evans index at the time of discharge, 3 and 6 months after shunt surgery. A favorable outcome is defined as shunt success with an improvement of more than 1 point in the NIHSS at the evaluation point. Evans index is tested thorough axial CT scan. Complication events throughout the study within 6 months after shunt implantation is investigated. Complication events occurring at any time within 6 months after cranioplasty are investigated.

SAEs occurring at any time is recorded to determine the safety, which is defined as death, an event that could lead to death, an event that require hospitalization or an extension of the hospitalization period, or disability, which is related to the treatment.

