### Data collection

2.14

The baseline characteristics and follow-up data will be collected by experienced and practiced assessors. The data collection form and the plan are shown in Table 1. Their family members will help them if they have difficulties in completing the evaluation. Any adverse events occurring during the study period are documented. Paper-based or electronic data will be recorded in the data collection form in time.

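### Assessor blinding is claimed for the whole trial, but the protocol's own procedures do not support it for shunt failure (primary) or the Evans index

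*Protocol article*

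**What the plan says.** Section 2.2 (Study design) says the trial "is a monocentric, assessor-blinded, non-randomized controlled trial", and the Abstract uses the same label. Section 2.7 (Randomizing and blinding) concedes that "It is not possible to blind participants to allocation" but then states that "data collection teams and analysts are blind to allocation and the intervention clinicians will not participate in any assessment". Neither section separates one outcome from another. Section 2.11 gives the evaluations at discharge, 3 months and 6 months to assessors other than the attending neurosurgeons.

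The procedures and outcomes that bear on the claim are these:

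- **VPS (2.9):** the lateral ventricle is reached through a scalp incision and a drilled skull opening. "The valve is placed at the cranial incision with a 3-point fixation to the subcutaneous tissue".
- **Lumboperitoneal shunt, LPS (2.10):** the catheter enters the lumbar spine. "The valve is placed at the frank region with a 3-point fixation to the subcutaneous tissue" (flank is evidently meant).
- **Evans index (2.13):** "Evans index is tested thorough axial CT scan".
- **Primary outcome (2.12):** shunt failure means clinical or radiological signs of several listed problems, a list that ends with "malfunction, or infection requiring shunt revision".
- **Data collection (2.14):** "Their family members will help them if they have difficulties in completing the evaluation".

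**The concern.** A reader takes an unqualified assessor-blinded label to cover the primary outcome. Here that outcome includes a treatment decision. Whoever decides that a shunt needs revision has to know which shunt is in place, and reports from unblinded patients feed into the decision. If the threshold for revising differs between the shunt types, the difference enters the primary comparison as a difference in failure rate.

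Two features of the plan make this more than a formality. Allocation is by self-selection or administrator selection (2.7), so randomization does not protect the comparison either. And the investigators plan on a large difference, 15% failure with VPS against 35% with LPS (2.6), so differing levels of suspicion are plausible. The report would nevertheless describe the assessment as blinded.

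**Working it through.** **1. The claim against each outcome**

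| Outcome | What the protocol describes | Can the assessor be blind? |
|---|---|---|
| Shunt failure (2.12) | Signs of a shunt problem, tied to revision | Not for the revision decision, by inference: it is a care decision about a known device |
| Evans index (2.13) | Axial CT of the head; only VPS leaves a ventricular catheter and a cranial valve (2.9, 2.10) | Not realistically. This follows from the catheter position; it is not stated |
| NIHSS, GCS, mRS (2.13) | Rated by staff other than the attending neurosurgeons; patients know their shunt and family may help (2.7, 2.11, 2.14) | Possible, if scars and valve sites are covered and nobody discloses |
| Statistical analysis (2.7) | Analysts stated to be blind | Possible with coded groups |

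**2. The plan's own figure**

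Inputs from 2.6: 15% and 35%, two-sided 5%, power 80%. The normal formula with unpooled variance gives

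n = (1.960 + 0.842)² × (0.15 × 0.85 + 0.35 × 0.65) / 0.20² = 69.7, so 70 per group.

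This reproduces the stated 70, read as per group, which the plan enlarges to 75. The sample size is not at issue here.

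**3. Illustration of what an open revision decision could do**

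The documents give no figure for this, so the following are assumptions: the true failure rate p is equal in both groups, and a fraction u of failures in one group is not revised and so not counted. The recorded rate in that group is p × (1 − u), against p in the other. The rejection probability is that of the uncorrected Pearson chi-squared test at 5%, summed exactly over both binomial distributions with 75 per group.

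| u | p = 15%: recorded rate | rejects | p = 25%: recorded rate | rejects |
|---|---|---|---|---|
| 0 | 15% | 5.1% | 25% | 4.9% |
| 10% | 13.5% | 5.9% | 22.5% | 6.4% |
| 20% | 12% | 8.4% | 20% | 11.2% |
| 30% | 10.5% | 13.0% | 17.5% | 20.1% |
| 40% | 9% | 20.4% | 15% | 33.6% |

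The 15% is the plan's VPS rate. The 25% is the midpoint of its two planning rates, (15% + 35%) / 2. With 10% unrevised the effect is slight; it becomes material only at the larger fractions.

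The bias could also hide a real difference. If the true rates are 15% and 35% but LPS failure is recorded at 30%, power with 75 per group falls from 82% to 60%.

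**The case against.** The strongest reply is that deciding to reoperate is clinical care and not outcome assessment. On that view the statement in 2.7 about the intervention clinicians is literally true, and what remains is a limit shared by any open surgical comparison with a revision-based endpoint. Part of this stands. The document never says who decides on revision, so a reader might infer that the treating neurosurgeons assess the primary outcome in breach of 2.7. The text does not support that reading. What it supports is narrower: the label is not limited by outcome, and blinding the assessors does not reach the revision decision.

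Other points also stand:

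- The revision clause in 2.12 is ambiguous. It may attach to infection only or to every listed problem, and it may mean that revision was needed or that it was performed. If it means needed, an assessor could in principle judge it.
- Breakage and tubing exposure are fairly objective, which limits the room for bias.
- CT and scar visibility mainly affect secondary outcomes. A flank valve lies under clothing, and the document does not say what assessors expose.
- The bias fractions have no source in the document.

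It might also be said that masking procedures belong in a fuller protocol. Their absence is not the point. The article makes a positive claim that its own procedures do not support for two outcomes.

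**Conclusion.** The point holds in limited form. The claim of assessor blinding in the Abstract, 2.2 and 2.7 is too broad. It is not supported for the Evans index, because the CT can reveal the shunt, or for shunt failure, because that depends on a decision presumably taken with the shunt type known. Both reasons are inferences, from the described catheter position and from the nature of a revision decision; neither is stated in the text.

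The documents do not support going further and calling all blinding void. The three clinical scales can be protected, and nothing refutes blinding of analysts. Nor do they support a prediction of bias of any particular size. The range of about 6% to 34% rejection is illustrative, and rests on equal true rates of 15% to 25% with 10% to 40% of failures unrevised in one group only. The sponsor should correct this, but the primary endpoint need not be replaced.

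**What to change.** 1. In 2.2 and 2.7, with the Abstract to match, restrict the blinding claim to NIHSS, GCS and mRS, and state that shunt failure and the Evans index are open-label.
2. Protect the scales: cover the scalp and flank at assessment visits, and ask patients and family members not to disclose the shunt type.
3. Keep the primary definition in 2.12, but state whether the revision clause applies to every listed problem and whether it means revision needed or revision performed.
4. Add two sensitivity analyses: (a) any shunt reoperation, taken from operative records whatever the recorded cause; (b) suspected failures that meet the listed signs but were not revised, counted as failures.

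Analysis (a) should not become the primary outcome. It would still depend on the open decision to operate, and it would depart from the failure definition behind the 15% and 35% planning rates. Classification of cause by the existing assessors from redacted summaries is not recommended either: they may already know the shunt type, and the site of failure can reveal it.

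The cost is a weaker blinding claim, coverings at visits, and some extra recording of unrevised suspected failures. No additional patients are needed and patient care does not change.

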### Intervention

2.8

Neurosurgeons with extensive experience in the procedure conduct both types of shunt implantation and they will be trained centrally in advance and reach uniform standard. Shunt system is obtained from Medtronic, Inc, Minnesota, USA. Initial pressure for the shunt system is set to the highest level (2.5 level) before surgery.^[15]^ Shunt function is checked when there is no improvement in clinical symptoms or when tight high-convexity and medial subarachnoid spaces, enlarged sylvian fissures, or acute callosal angles were observed.^[16]^ The pressure setting is lowered by 1 step (0.5 level) with careful consideration of the patient's safety.

### VPS

2.9

VPS implantation is conducted under general anesthesia and the patients are positioned in the supine position with the head turned to the left. Access to the lateral ventricle is obtained through scalp incision, skull drilling, and dura incision. Peritoneal access is obtained via a minimal invasive incision or split trocar access. A subcutaneous tunneler is passed from the abdominal incision to the cranial incision. The valve is placed at the cranial incision with a 3-point fixation to the subcutaneous tissue. Once the cranial catheter is connected to the valve and the valve is connected to the peritoneal tubing with confirmation of adequate CSF flow, the peritoneal catheter is inserted into the peritoneal space.

### LPS

2.10

LPS implantation is conducted under general anesthesia and the patients are positioned in the lateral position. A lumbar catheter is inserted through the L3/4 or L2/3 interlaminar space into the spinal subarachnoid space. The catheter was then placed in a subcutaneous pocket made at the flank region. Peritoneal access is obtained via a minimal invasive incision or split trocar access. A tunneler is passed from the abdominal incision to the flank region, and then to the lumbar incision. The valve is placed at the frank region with a 3-point fixation to the subcutaneous tissue. Once the lumbar catheter is connected to the valve and the valve is connected to the peritoneal tubing with confirmation of adequate CSF flow, the peritoneal catheter is inserted into the peritoneal space.

### Outcomes

2.11

As shown in Table 1, each participant is evaluated before surgery, at the time of discharge, and 3 and 6 months after surgery by experienced and practiced assessors other than the attending neurosurgeons, including neurologists, psychiatrists, clinical psychologists, and physical therapists.

**Table 1 T1:**
[figure not shown]
Study schedule.

### Primary outcome

2.12

The primary outcome is the rate of shunt failure 6 months after shunt surgery. According to previous study, shunt failure is defined as the occurrence of clinical or radiological signs of shunt obstruction, breakage, tubing exposure, malfunction, or infection requiring shunt revision. Shunt success is defined as the absence of shunt failure.

### Secondary outcomes

2.13

The secondary outcomes include NIHSS, CGS, mRS, and Evans index at the time of discharge, 3 and 6 months after shunt surgery. A favorable outcome is defined as shunt success with an improvement of more than 1 point in the NIHSS at the evaluation point. Evans index is tested thorough axial CT scan. Complication events throughout the study within 6 months after shunt implantation is investigated. Complication events occurring at any time within 6 months after cranioplasty are investigated.

SAEs occurring at any time is recorded to determine the safety, which is defined as death, an event that could lead to death, an event that require hospitalization or an extension of the hospitalization period, or disability, which is related to the treatment.

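### The SAE definition carries a relatedness condition, so serious events judged unrelated can drop out of the safety comparison, and the sentence can be read in two ways.

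*Protocol article*

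**What the plan says.** The Secondary outcomes section (2.13) of the protocol article gives the purpose of the SAE record: "SAEs occurring at any time is recorded to determine the safety". It then defines an SAE as death, an event that could lead to death, and "an event that require hospitalization or an extension of the hospitalization period, or disability, which is related to the treatment".

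Three other statements bear on the point and carry no relatedness condition:

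- Study design (2.2): "A serious adverse events (SAEs) throughout the study are recorded regarding the safety of shunts".
- Data collection (2.14): "Any adverse events occurring during the study period are documented".
- Secondary outcomes (2.13), on complications: "Complication events throughout the study within 6 months after shunt implantation is investigated".

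Randomizing and blinding (2.7) says that groups are formed "according to self-selection or administrator selection rather than through randomization". On blinding it says "It is not possible to blind participants to allocation", but also that "data collection teams and analysts are blind to allocation and the intervention clinicians will not participate in any assessment". No section says who decides whether an event is related to the treatment.

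**The concern.** How serious an event is and what caused it are two separate judgments. The first can be made from what happened to the patient; the second is an opinion. A definition that needs both makes the SAE count depend on the opinion.

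That opinion is hard to form in this trial. The patients have all had an intracranial hemorrhage, so a later admission or death may come from the underlying disease, the shunt or both. The two operations also differ: one enters the lateral ventricle, the other the lumbar subarachnoid space. Attributing an event to a particular operation is hard without knowing which was done, and the same event may be attributed more readily to one than to the other.

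Efficacy and safety are both stated objectives (section 2.1). If relatedness is judged differently in the two groups, the SAE comparison can show a difference that does not exist or hide one that does. If it is judged alike, the count is still too low in both.

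**Working it through.** **1. The two readings of the definition.** The closing clause can attach to the whole list or only to its last item.

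| Serious event judged unrelated | Clause covers the whole list | Clause covers disability only |
|---|---|---|
| Death | not an SAE | SAE |
| Event that could lead to death | not an SAE | SAE |
| Hospitalization or its extension | not an SAE | SAE |
| Disability | not an SAE | not an SAE |

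The comma before the clause favors the first reading, but the grammar does not settle it. Under the second, disability alone is filtered and no reason is given. Two careful readers could produce different SAE tables from the same data.

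**2. What happens to an excluded event.** Sections 2.14 and 2.13 capture all adverse events, and complications to 6 months, whatever the cause. An unrelated death therefore stays in the trial record. It leaves only the count labeled SAE, which is the count that section 2.13 assigns to judging safety.

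**3. Size, on assumed values.** The article gives no SAE rate and no attribution rate, so no figure in the document is available to reproduce or correct. Inputs:

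- n = 75 per group (Sample size, 2.6).
- Two-sided 5% test (sections 2.6 and 2.16); chi-squared without continuity correction, the rejection probability summed exactly over the two binomial distributions.
- Assumed: true risk of a serious event 20% in both groups, that is 75 × 0.20 = 15 patients per group.
- Assumed: proportions a and b of these events judged related in the two groups.

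Apparent SAE rate = 0.20 × a in one group and 0.20 × b in the other.

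| Judged related (a vs b) | Apparent SAE rates | Apparent difference | Probability of p < 0.05 |
|---|---|---|---|
| No filter (100% vs 100%) | 20% vs 20% | 0 points | 0.051 |
| 70% vs 70% | 14% vs 14% | 0 points | 0.051 |
| 70% vs 80% | 14% vs 16% | 2 points | 0.065 |
| 60% vs 80% | 12% vs 16% | 4 points | 0.109 |
| 50% vs 80% | 10% vs 16% | 6 points | 0.193 |

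Because the true risks are equal, each probability is a false-positive rate. With equal attribution of 70% the test keeps its level, but 1 − 0.70 = 30% of serious events leave the count: 15 × 0.30 = 4.5 patients per group on average.

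**The case against.** The strongest objection is blinding. A reader might infer that the causality call is made by staff who know the shunt type. The article does not support this. It describes the trial as assessor-blinded, blinds data collectors and analysts, and keeps the operating clinicians out of every assessment; only the participants are said to be unblinded. What remains is that no judge of relatedness is named, and that the judgment is hard to make blind. The defect also does not depend on unblinding, since a fully blinded judge would still remove events from the count.

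A reader might also infer that deaths are hidden, or that the data monitoring committee sees only filtered events. Neither follows. All adverse events are documented, and section 2.15 has the committee review the study data without limiting that review to SAEs as defined.

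Third, the illustration rests on chosen values. That is correct. The figure of 0.193 is the largest of the cases shown, and the excess nearly vanishes when attribution differs by only 10 points.

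Finally, an article may leave causality forms and table layouts to the full protocol or analysis plan, and section 2.16 names no test specific to SAEs. That limits the weight of the point. It does not remove it, because the definition itself is stated in the article.

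**Conclusion.** The point holds as a fault in a stated definition. Section 2.13 merges seriousness with relatedness and does so in a sentence with two readings. On the natural reading, any serious event judged unrelated leaves the SAE comparison; on the narrower one, only disability does. The events remain in the trial record.

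The size cannot be derived from the document. With an assumed true risk of 20% in both groups and 75 per group, attribution that differs by 10 to 30 percentage points raises the false-positive rate from about 0.05 to between 0.065 and 0.193. Equal attribution of 70% leaves the test level alone but undercounts serious events by 30%. These figures assume the whole-list reading. They show what differential attribution could do, not that it will occur.

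The primary outcome, shunt failure, and the sample size are not affected. The wording should be changed because safety is a stated objective and the change is cheap.

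**What to change.** In section 2.13:

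- Delete the closing relatedness clause, so that an SAE is defined by seriousness alone. This also removes the ambiguity and agrees with sections 2.2 and 2.14.
- Compare all SAEs by group, whatever their cause.
- Record relatedness as a separate field. Name who assesses it, and where possible have it done by someone blind to allocation.
- Show related SAEs as a second display.
- Report all-cause death by group.

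The cost is one clause and one form field. The downside is that slightly more events will count as SAEs; the extra recording is small because all adverse events are already to be documented. Treatment and sample size do not change.
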